### Participants

Participants will be recruited from the “Koutsochero” refugee camp in the municipality of Larissa. Approximately 1500 residents live in this camp. In March 2020, 916 residents were aged from 16 to 59 years (62% men, 38% women). The population is diverse in terms of socio-demographic background. Most of the residents are from Syria (36%), Afghanistan (34%) and Iraq (14%), whereas the remaining 16% are from the Middle East or from the sub-Saharan region.

To estimate the minimal sample size, a power analysis was carried out using G*Power 3.1. Based on the pilot study of Knappe et al. [23], a weak-to-moderate effect can be expected on our primary outcome (PTSD symptoms; *f* = 0.19). However, in the pilot study, only males and a short-term intervention (8 weeks) were considered, and no longer-term follow-ups were carried out. Therefore, we do not know whether similarly strong effects would be found in women and whether similarly strong effects can be observed after a longer follow-up period. As a consequence, we have decided to use a slightly more conservative effect size estimate (*f* = 0.15). The mean difference in the primary outcome variable (immediately post) will be used as primary endpoint. With an α-error probability of 5%, a power of 0.8, three measurement timepoints (*r* = 0.5 between repeated measures) and four groups (one male and female IG and WLCG), a total number of 108 participants is needed. With an expected dropout rate of 25%, a total of 136 participants will be recruited (68 men, 68 women), with half of them being randomly assigned to the IG or WLCG. The expected dropout rate is based on our pilot study (16%) [23] and a meta-analysis in patients with major depression (15% in a more controlled/clinical setting) [31].

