#### Self-reported data

PTSD symptoms (primary outcome) will be assessed with the 22-item Impact of Event Scale-Revised (IES-R) [40]. The instrument is internationally accepted, not culturally specific, and is available in English [40], Arabic [41], Farsi [42], French [43] and Greek [44]. The IES-R items refer to DSM-V and ICD-10 criteria of PTSD. The IES-R has been used previously in refugee populations [45]. The IES-R provides a cut-off for a possible PTSD diagnosis [46]. In our pilot study [23], the IES-R had good internal consistency.

Perceived stress during the past month will be assessed with the 10-item Perceived Stress Scale (PSS) [47]. Participants will be asked how often they find their lives to be overwhelming, uncontrollable and unpredictable. The PSS is available in English [47], Arabic [48], Farsi [49], French [50] and Greek [51], and has been used in refugee populations [52].

Depressive symptoms will be assessed with the 9-item Patient Health Questionnaire (PHQ-9) [53]. Items of this instrument refer to DSM-V criteria for major depression. The PHQ-9 has been previously employed with refugee populations [54]. The instrument exists in English [53], Arabic [55], Farsi [56], French [57] and Greek [58].

Anxiety symptoms will be assessed with the 7-item General Anxiety Disorder (GAD-7) scale [59]. The GAD-7 exists in Arabic [55], Farsi [60], French [61] and Greek [62], and has been used previously with refugees [63].

Insomnia symptoms will be assessed with the Insomnia Severity Index (ISI) [64], a brief screening measure of insomnia and an outcome measure in treatment research, which takes into consideration the criteria for insomnia of the DSM-V [65]. Arabic [66], Farsi [67], French [64] and Greek [68] versions of the ISI exist, and the instrument has been used previously with refugees [69].

Health-related quality of life will be assessed with the five-item World Health Organization Index (WHO-5) [70], which is specifically designed for psychiatric populations [71]. The instrument exists in English [70], Arabic [72], Farsi [73], French [74] and Greek (see https://www.psykiatri-regionh.dk/who-5/who-5-questionnaires/Pages/default.aspx), and has been used with refugees previously [75].

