### Analysis of quantitative data

#### Inspection of raw data

Data will be first inspected for missing values. Based on the nature of missingness, appropriate methods will be used to substitute missing data (see below). Data will also be screened for uni- and multivariate outliers, the latter using the Mahalanobis distance criterion. Appropriate methods to deal with uni- and multivariate outliers will be applied (replacement, transformation and/or exclusion) [106]. Before presenting the descriptive statistics, the distribution of the variables will be tested with Kolmogorov-Smirnov and Shapiro-Wilk tests.

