#### Effects of the intervention

Multilevel modelling will be used to evaluate the effects of the intervention. The longitudinal analyses will be performed with linear mixed models (random effects). The within-person parameters (intercepts and slopes of outcome variables) at Level 1 will be conceptualized as dependent variables in Level 2 (between-person). Treatment conditions (as well as potential covariates) will be integrated as Level 2 predictor(s) to detect and explain between-person change over time [107]. In case of potential violation of prerequisites (e.g. non-normality of data) mixed logistic regression models will be applied.

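### The fallback to mixed logistic regression on non-normality does not suit continuous scores and would replace the declared mean-difference endpoint with an odds ratio on an undefined categorisation

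*Protocol article*

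**What the plan says.** Four places in the protocol article bear on this.

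- **Effects of the intervention**, main analysis: "The longitudinal analyses will be performed with linear mixed models (random effects"), with treatment condition as a between-person predictor.
- **Effects of the intervention**, fallback: "In case of potential violation of prerequisites (e.g. non-normality of data) mixed logistic regression models will be applied". The section gives no outcome coding, cut-point or threshold for the switch.
- **Participants**, sample size paragraph: "The mean difference in the primary outcome variable (immediately post) will be used as primary endpoint". The calculation uses an effect size f of 0.15 and yields 108 participants, raised to 136 for dropout.
- **Inspection of raw data**: before descriptive statistics are presented, "the distribution of the variables will be tested with Kolmogorov-Smirnov and Shapiro-Wilk tests". This section does not mention the choice of model.

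The primary outcome is the 22-item IES-R. Under Self-reported data the article notes "The IES-R provides a cut-off for a possible PTSD diagnosis [46"], but it states no value and does not connect the cut-off to the fallback.

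**The concern.** A logistic model describes a categorical outcome. The IES-R score, estimated VO2max, lipids, hs-CRP and reaction times do not become categorical because their distribution is skewed. Non-normality of a continuous outcome is usually met by examining residuals, using robust or resampling-based inference, or transforming. Changing the type of outcome is a different step.

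Three things are at stake for the primary analysis:

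1. **The estimand.** A mean difference becomes an odds ratio, on a categorisation that is not given.
2. **The sample size.** It was derived for a continuous comparison, and no power is stated for a logistic one.
3. **Pre-specification.** The condition is only a potential violation, with no criterion. The model, and any cut-point, could be settled after the outcome data have been inspected.

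**Working it through.** **1. What the sample size was derived for.** Inputs from the Participants section: f = 0.15, α = 5%, power 0.80, m = 3 timepoints, correlation ρ = 0.5, k = 4 groups. The within-between interaction of a repeated-measures ANOVA has

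λ = f² × N × m / (1 − ρ), df1 = (k − 1)(m − 1) = 6, df2 = (N − k)(m − 1).

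- N = 104: λ = 0.0225 × 104 × 3 / 0.5 = 14.04, df2 = 200, power 0.799.
- N = 108: λ = 0.0225 × 108 × 3 / 0.5 = 14.58, df2 = 208, power 0.817.

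So 108 is the first multiple of 4 to reach 0.80, and the stated figure reproduces exactly. It rests on a continuous outcome throughout.

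**2. Is the switch needed for validity?** A plain two-group comparison of means was simulated with 54 per arm (108 / 2) and no true effect, on exponential, lognormal and gamma outcomes. The two-sided 5% test rejected in 4.3% to 5.0% of runs. At this size, skewness of that kind did not inflate the type I error.

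**3. Illustration of the power cost, normal score.** This step rests on assumptions: one timepoint, a two-sided 5% test, a binary split, and an effect set so that the continuous comparison has 80% power. The two arm sizes are 54 (108 / 2) and 51 (136 × 0.75 = 102, halved).

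- Effect: d = (1.960 + 0.842) × √(2/n), which is 0.539 at n = 54 and 0.555 at n = 51.
- With a share p₁ of controls above the cut, the share in the intervention arm is p₂ = Φ(Φ⁻¹(p₁) − d).
- Power = Φ[(p₁ − p₂ − 1.96 × SE₀) / SE₁], where SE₀ = √(2p̄(1 − p̄)/n), p̄ = (p₁ + p₂)/2 and SE₁ = √([p₁(1 − p₁) + p₂(1 − p₂)]/n).

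Worked at n = 54 and p₁ = 0.50: p₂ = 0.295, SE₀ = 0.0942, SE₁ = 0.0921. Power = Φ[(0.2051 − 0.1847)/0.0921] = 0.588.

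| Controls above cut | Power, 54 per arm | Power, 51 per arm | Relative loss from 0.80 (54 per arm) |
|---|---|---|---|
| 50% | 0.588 | 0.587 | 26% |
| 33% | 0.518 | 0.515 | 35% |
| 25% | 0.458 | 0.455 | 43% |
| 20% | 0.409 | 0.405 | 49% |
| 75% | 0.573 | 0.573 | 28% |

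A baseline-adjusted simulation (correlation 0.5, 54 per arm, 2,000 runs) gave power 0.79 for the linear model. The logistic model had 0.52 to 0.54 at a 50% cut and 0.42 to 0.43 at a 25% cut.

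**4. The same comparison for non-normal shapes.** The fallback is meant for non-normal data, so step 3 is not the case that would arise. With 54 per arm, 8,000 runs, a shift effect and 20% to 75% of controls above the cut, the relative loss was:

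| Shape | Relative loss of power (negative = gain) |
|---|---|
| Gamma, skewness 1 | 7% to 66% |
| Gamma, skewness 1.4 | −3% to 68% |
| Lognormal | −8% to 68% |
| Left-skewed gamma | −2% to 36% |
| t with 5 df | 5% to 48% |
| Laplace | −15% to 55% |

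The result depends on the shape and the cut. The document fixes neither.

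**The case against.** The strongest defence is that this is one contingency sentence attached to an appropriate main model, and that fallback details usually go into an analysis plan that is not shown. That answers a complaint about missing detail. It does not answer this point, because the sentence states a rule, and a more detailed version of the rule would still depart from the mean-difference endpoint.

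Three stronger readings are tempting, and the document does not support them.

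- **That the Kolmogorov-Smirnov and Shapiro-Wilk tests trigger the switch, and will fire for most questionnaire scores.** They are the only normality checks named, but the text places them before the descriptive statistics and does not tie them to the choice of model. The prerequisites in the fallback could include residuals. The firing rate is also unknown. Assuming a 0 to 88 score with mean 30 to 45 and SD 18 to 20, Shapiro-Wilk rejects in about 41% to 100% of samples at n = 136 and 26% to 99% at n = 102. The article gives no IES-R mean, SD or range.
- **That a dichotomy is forced.** The text does not say binary. An ordinal logistic model could fit a bounded sum score without a single cut and would lose less power. The text does not mention one, however, and it would also abandon the mean difference. For the IES-R a published cut-off exists, so a binary version need not be arbitrary, but the fallback does not adopt it.
- **That the switch costs a quarter to a half of the power.** This holds only for a normal score split at assumed cuts.

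**Conclusion.** The point stands as a fault in what the article states. Following the sentence as written would answer non-normality with a model for a different kind of outcome. It would replace the declared primary endpoint with an odds ratio on an undefined categorisation, outside the basis of the sample size, and leave the choice of primary analysis open until the data are seen. These conclusions need no distributional assumption.

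No single figure for lost power should be attached to it. The fall from 80% to about 59% or 41% is conditional on a normal score, a binary split, an effect solved back from 80% power, and half or a fifth of controls above the cut. For the non-normal shapes tried, the change ran from a 15% relative gain to a 68% relative loss. The linear mixed model itself is not in question.

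**What to change.** Delete the logistic fallback for continuous and multi-item outcomes, and state instead:

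- The linear mixed model for the post-intervention mean difference in IES-R is the primary analysis, whatever any normality test shows.
- Model assumptions are checked on residuals. Marked departures are handled with robust or bootstrap confidence intervals or, for skewed secondary markers, a transformation named in advance.
- Logistic models are used only for secondary outcomes that are binary by design, such as the IES-R cut-off, with the cut fixed in advance.

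The descriptive normality tests may stay, provided they do not drive the choice of model. The cost is wording only, with no change to data collection or sample size. It should be settled and dated before outcomes are compared by arm.

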#### Dropout analyses and missing data handling

Before testing our main hypothesis, we will test whether those participants who completed all data assessments and those who dropped out after the first or the second data assessment differ with regard to their socio-demographic background or in one of the assessed study variables. In case of systematic differences, one can assume missing not at random (NMAR) and main analyses will be replicated using intent to treat techniques (e.g. last observation carried forward) to estimate the influence of dropout on the results. In any other case, missing data will be treated as random (MAR) and the multilevel modelling will be adapted whether by integrating obvious missing patterns (like dropout) as additional Level 2 predictor and/or by imputing missing data (FIML) for missing data without identifiable patterns [108].

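### The dropout rule infers NMAR from differences on observed variables and checks it with LOCF, so the planned dropout check can mislead

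*Protocol article*

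**What the plan says.** All of this is in the Protocol article.

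- **Trigger.** Under *Dropout analyses and missing data handling*, completers are compared with those who leave after the first or second assessment, to see whether they "differ with regard to their socio-demographic background or in one of the assessed study variables".
- **Difference found.** "In case of systematic differences, one can assume missing not at random (NMAR) and main analyses will be replicated using intent to treat techniques", with one example of such a technique and its purpose: "e.g. last observation carried forward) to estimate the influence of dropout on the results".
- **No difference found.** "In any other case, missing data will be treated as random (MAR"). The multilevel model is then adapted by "integrating obvious missing patterns (like dropout) as additional Level 2 predictor and/or by imputing missing data (FIML").
- **Main model.** Under *Effects of the intervention*: "The longitudinal analyses will be performed with linear mixed models (random effects").
- **Amount of dropout.** Under *Participants*: "With an expected dropout rate of 25" per cent, 136 people are recruited. The rates cited in support are 16% (pilot study) and 15% (a meta-analysis in major depression). The primary endpoint is the mean difference immediately after the intervention.

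**The concern.** The rule goes wrong at three points.

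1. **The inference.** Every variable in the comparison is observed. A difference shows that dropout is not completely at random. Dropout that depends on observed variables is what MAR allows. NMAR means that dropout depends on the unseen values themselves, and no comparison of observed variables can show that.
2. **The response.** LOCF assumes that a person who leaves stays at the last recorded score. That is not a model for NMAR, and its estimate is in general biased even when the data are MAR. Intent-to-treat says who is analysed and in which arm. It is not a way of filling in values.
3. **The placement of the other tools.** FIML is valid under MAR, so it is useful precisely when dropout is related to observed variables. It is mentioned only where no such relation is found. Dropout status is known only after randomisation and belongs to pattern-mixture modelling for NMAR, yet it may be added to the main model in the MAR branch.

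At stake is what the trial can say about dropout. Informative dropout is plausible in this setting, since the Discussion lists refugee departures among the barriers. The only named check could make a real effect look fragile, or lend support to a null one, for reasons unrelated to informative dropout.

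**Working it through.** The plan gives no figure for this point. The only figures to use are the dropout rates under *Participants*: the 25% allowance (0.25 × 136 = 34 people) and the cited 16% and 15%.

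**Step 1. Logic.** Write R for remaining in the study.

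- Missing completely at random: R is unrelated to any outcome or covariate.
- MAR: R may depend on observed data.
- NMAR: R depends on unobserved values even after conditioning on observed data.

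The comparison asks whether R is related to observed data. A yes rejects only the first. A no does not rule out the third.

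**Step 2. What LOCF does at the post assessment.** Let D be the true benefit (lower IES-R is better), c the change common to both arms, and dI and dW the proportions of the intervention and wait-list arms lost before post. LOCF sets the change of those people to zero. If they would otherwise have changed like the rest of their arm, the expected LOCF difference is

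(1 − dI)(c − D) − (1 − dW)c = −(1 − dI)D − c(dI − dW).

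- Equal dropout d: the result is −(1 − d)D. At d = 0.15, 0.16 and 0.25 the factor is 0.85, 0.84 and 0.75, a loss of 15%, 16% and 25%, whatever D is.
- Unequal dropout adds the term −c(dI − dW), whose sign depends on the drift and on which arm loses more.

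**Step 3. Simulation under MAR.** These values are assumed and are not in the documents: SD 1, D = 0.30 SD or 0, drift c = 0 or ±0.3 SD, and dropout of 35% in one arm and 15% in the other. The correlation of 0.5 and the 25% average dropout are the protocol's. Dropout depends only on arm and observed baseline score. The MAR-valid comparator is a regression of observed post scores on arm and baseline.

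| D | c | dI / dW | Formula | LOCF, simulated | MAR-valid, simulated |
|---|---|---|---|---|---|
| 0.30 | 0 | 25% / 25% | −0.225 | −0.228 | −0.305 |
| 0.30 | −0.3 | 35% / 15% | −0.135 | −0.107 | −0.296 |
| 0.30 | −0.3 | 15% / 35% | −0.315 | −0.337 | −0.298 |
| 0 | −0.3 | 35% / 15% | +0.06 | +0.078 | −0.005 |
| 0 | −0.3 | 15% / 35% | −0.06 | −0.082 | +0.002 |
| 0 | +0.3 | 35% / 15% | −0.06 | −0.033 | +0.004 |

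Formula and simulation differ by about 0.02 to 0.03 when dropout is unequal. In the simulation people with higher baseline scores leave more often, so regression to the mean adds to the LOCF error. With D = 0 and c = 0, LOCF gives +0.024 at 35%/15%. The MAR-valid analysis stays within about 0.005 SD of the truth.

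At N = 136, with 35%/15% dropout and c = −0.3:

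- D = 0: LOCF rejects at the 5% level in 9.5% of trials, against 5.2% for the MAR-valid analysis.
- D = 0.30: the rejection rates are 12% and 40%.

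**Step 4. The trigger.** Assume dropout completely at random (34 of 136) and tests at 5%. At least one difference arises by chance with probability 1 − 0.95^10 = 40% for 10 independent tests and 1 − 0.95^30 = 79% for 30. At correlation 0.5 between variables, the simulated figures are 30% and 52%. The number of tests and the level are assumptions.

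**The case against.** The strongest case on the other side is that the text describes a second run of the main analyses, made only if dropouts differ, with LOCF as an example. The mixed model is still fitted and nothing replaces it. That stands. A reader might infer that the rule switches the trial to LOCF and so biases the treatment estimate. The wording does not support this.

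Three further points have weight.

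- **The 25% is an allowance over a three-assessment study.** People who leave after the second assessment have the primary endpoint observed, and the cited rates are 16% and 15%. A reader might infer that a quarter of the primary outcome will be missing. The protocol does not say so, and a 25% loss of effect is an upper end.
- **The dropout term is optional**, being joined to FIML by and/or, and conditioning on dropout pattern can be legitimate in a pattern-mixture model averaged over patterns. A reader might infer that the term destroys the randomised comparison. That depends on model terms that the article does not give. What remains is that a post-randomisation variable is allowed into the main model, in the branch labelled MAR.
- **Treating data as MAR when no difference appears is a working assumption**, not a claim of proof. That also stands.

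Covariate lists and imputation settings may properly sit in an analysis plan that is not shown. The inference to NMAR and the description of LOCF as intent-to-treat are different: they are stated in the article and are wrong as stated.

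**Conclusion.** The point holds for the dropout rule, not for the main estimate. The comparison cannot establish NMAR, and the one technique named to gauge the influence of dropout does not address NMAR. LOCF understates the effect by the factor 1 − d under equal dropout d before post: 15% to 25% across the rates the protocol cites, with 25% only if the whole allowance is lost before that assessment. This assumes that those lost would have changed like the rest of their arm. Under unequal dropout and a common drift, both assumed, the LOCF error can go towards or away from the null.

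The consequence is a sensitivity analysis that can mislead. The rule does not say which result prevails if it disagrees with the mixed model, and it prescribes no NMAR check where no difference is found.

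**What to change.** Rewrite the section on dropout and missing data as follows.

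1. Keep the likelihood-based mixed model on all randomised participants, under MAR, as the main result whatever the completer–dropout comparison shows. Add observed baseline predictors of dropout.
2. Report the completer–dropout comparison descriptively only.
3. Delete the inference to NMAR, delete LOCF, and reserve intent-to-treat for the analysis of everyone as randomised.
4. Take dropout pattern ("integrating obvious missing patterns (like dropout) as additional Level 2 predictor") out of the main model. Use it, if at all, in a pattern-mixture sensitivity analysis averaged over patterns.
5. Always run one NMAR sensitivity analysis, by delta-adjusted or reference-based imputation, and state that it qualifies the main result and does not compete with it.

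The cost is a text change and one extra analysis, with no new data.

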### Qualitative data collection

To tackle the described research questions, a mixed methods approach in terms of data collection is adopted [109]. This mixed methods approach consists of qualitative methods combined with quantitative elements. Data will be collected and analysed using methodological triangulation [110]. The research design will allow for a systematic comparison over time. Free-listing, focus group discussions (FGD) and qualitative semi-structured interviews will be used as data collection methods.

Free-listing is a useful screening tool that identifies relevant issues for the target group within a short time span. An interviewer will ask a primary question designed to elicit a list. The interviewee can then choose the most relevant items in the list for further study and set his/her priorities. The advantage of free-listing involves the assessment of key problems from different perspectives, including vulnerable and marginalized persons. Free-listing does also avoid the risk of inhibiting or influencing group dynamics and is a good entry point for a key informant interview.

Focus group discussion (FGD) is a systematic method to gather people (chosen according to gender, age, function, ethnic background, etc.) to discuss specific topics. The group is guided by a researcher who introduces discussion points. He or she supports the participants to engage in a lively and natural discussion where opinions can be freely expressed. The FGD offers an opportunity for participants to directly interact, to agree or disagree with each other. This method provides insights on group dynamics, hierarchies and the range of inherent opinion and ideas. This method allows for inconsistencies and dissonance within particular groups or communities to become more obvious.

Qualitative semi-structured interview with key informants who have first-hand knowledge about the camp or specific issues provide a holistic and in-depth perspective. These key informants or experts with particular knowledge provide insights on challenges, contradictions and/or opportunities. This method reflects the subjective and personal opinion of an individual and/or the function she/he holds. Translation must be assured to assure smooth communication.

